### Secondary outcome measures

(I) Lower limb strength and balance determined by timed up and go (TUG) test. Record the time the following process takes: stand up from a standard seat (seat height is approximately 46 cm, armrest height is 65 cm), walk 3 m away then turn around, walk back to the chair, and sit down [42–44]. (ii) 6-min walk test (6MWT): In an outdoor closed corridor (30 m), participants were allowed to walk back and forth. The timer is set to 6 min, and total walking distance is measured. Participants are allowed to slow down and stop to rest if necessary but are encouraged to continue walking [42, 45]. (iii) Short Form 36 Item Health Survey (SF-36) includes 8 dimensions: physical function, physiological function, physical pain, general health, vitality, social function, emotional function, and mental health, with a total of 36 questions. The total score ranges from 0 to 100. A higher total score indicates a higher quality of life [46, 47].

### Safety measure

Since the majority of the interventions are physical exercises, there is no anticipated harm and compensation for trial participation. Participants will be monitored for any adverse events during the intervention, which will be collected and recorded on the case report form (CRF). All adverse events and abnormal laboratory parameters will be followed up until normal, abnormal clinical significance or return to the pretreatment state.

### Sample size

The calculation is carried out according to the unified standard of clinical trial reporting and the calculation requirements of the sample size of noninferiority experiments [41, 48]. Based on the previous research results of our research team and comprehensive consideration of previous experience [28], the reduction in pain score in the WOMAC scale was used to assess the improvement of KOA symptoms. The average pain scores in patients with KOA were 1.65, 1.7, and 0 respectively [36, 49]. We set a to 0.05 and test power 1-β to 90%. Calculation via G*Power 3.1 software. A total of 33 participants is required for the calculation. With allowance for a dropout rate of 20%, each group requires 14 enrolled participants.

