**Discussion:**

The findings from this trial will establish the feasibility and effectiveness of IoT-based power cycling and neuromuscular training on elderly patients with KOA in the community. As a result, this trial may help provide experimental evidence for finding a better exercise method suitable for elderly patients with KOA in the community.

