## Methods

### Aim

The primary objective of this study is to compare the effect of IoT-based power cycling and neuromuscular training on the elderly patients with KOA in the community. Whether the intervention of elderly patients with KOA is effective or not provides experimental evidence for finding a better exercise delivery mode for elderly patients with KOA in the community.

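### The sample size is labelled noninferiority but the planned analysis tests differences, and the stated 90% power does not cover cycling versus neuromuscular training (about 5% at the assumed means)

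*Protocol article*

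**What the plan says.** **Sample size.** The section states that sizing follows "the calculation requirements of the sample size of noninferiority experiments". The endpoint is fixed by "the reduction in pain score in the WOMAC scale was used to assess the improvement of KOA symptoms". The planning values are "The average pain scores in patients with KOA were 1.65, 1.7, and 0 respectively", with no arm named for each value. Error rates are given as "We set a to 0.05 and test power 1-β to 90" per cent, and the tool as "Calculation via G*Power 3.1 software". The result is "A total of 33 participants is required for the calculation", raised to 14 per group (42 in all) for 20% dropout. No margin, SD, effect size or test is named.

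**Statistical analysis.** All tests are at 0.05. The inferential methods are repeated-measures analysis of variance or, if its assumptions fail, the Kruskal–Wallis test. Both are tests for a difference.

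**Aim and Abstract.** The Aim reads "The primary objective of this study is to compare the effect of IoT-based power cycling and neuromuscular training", and the Abstract's Discussion hopes for help in "finding a better exercise method suitable for elderly patients with KOA in the community". The Abstract's Methods, however, describe the comparison as the two exercise groups against the control group.

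**The concern.** Three statements that should agree do not: the hypothesis type (noninferiority in one section, difference in another), the main contrast (exercise versus exercise in the Aim, exercise versus control in the Abstract), and the comparison to which the 90% belongs.

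The practical risk lies in how the result is read. If the two exercise programmes perform as assumed, a test between them will be non-significant about 95% of the time. With a noninferiority label on the sample size, that result could be reported as showing the programmes to be equally good. The stated 90% would seem to support that reading, although the data could not.

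**Working it through.** **Inputs.** From Sample size: means 1.65, 1.7 and 0; alpha 0.05; power 90%; total 33, so 11 per arm under the 1:1:1 allocation in Randomization and allocation; 14 per arm enrolled. Assumptions: the means are in the order cycling, neuromuscular, control; tests are two-sided unless stated. The SD is not given, so it is back-solved below.

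**1. Can 33 be reproduced?** Not from the stated inputs alone, because the SD is missing. As a one-way ANOVA on change:
- Grand mean = (1.65 + 1.7 + 0)/3 = 1.1167.
- Between-group sum of squares = 0.5333² + 0.5833² + 1.1167² = 1.872.
- SD of the means = √(1.872/3) = 0.790, and f = 0.790/SD.
- With the noncentral F (2 and N − 3 df, noncentrality N·f²), 33 is the smallest balanced total with 90% power when the SD lies between 1.149 and 1.212 (f from 0.688 down to 0.652). At SD 1.2, power is 90.6%. SD 1.0 would give N = 24, and SD 1.5 would give N = 51.

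Other routes also reach 33. A two-group comparison of 1.65 with 0 gives 11 per arm at SD 1.15 (normal approximation). A repeated-measures between-group test over four time points fits with SD 1.38 to 1.76 (correlation 0.7 to 0.3). The ANOVA form is therefore an inference.

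The dropout step reproduces: 33/0.8 = 41.25, rounded up to 42, or 14 per arm.

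**2. Where does the signal come from?** The exercise-versus-exercise contrast contributes 0.05²/2 = 0.00125 of the 1.872, less than 0.1%. The rest is the distance of the control mean from the two exercise means.

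**3. Power by contrast.** Two-sample t test, n per arm, noncentrality (d/SD)·√(n/2):

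| Contrast | Difference | n per arm | SD 1.149 | SD 1.212 |
|---|---|---|---|---|
| Cycling vs neuromuscular | 0.05 | 11 | 5.1% | 5.1% |
| Cycling vs neuromuscular | 0.05 | 14 | 5.1% | 5.1% |
| Cycling vs control | 1.65 | 11 | 89% | 86% |
| Neuromuscular vs control | 1.70 | 11 | 91% | 88% |
| Cycling vs control, alpha 0.025 | 1.65 | 11 | 82% | 77% |
| Neuromuscular vs control, alpha 0.025 | 1.70 | 11 | 84% | 80% |
| Cycling vs control | 1.65 | 14 | 96% | 93% |
| Neuromuscular vs control | 1.70 | 14 | 96% | 95% |

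The first result hardly depends on the SD: with 11 or 14 per arm it is 5.0% to 5.8% for any SD from 0.5 to 4.

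**4. Precision for cycling versus neuromuscular training.** The 95% CI half-width is t(0.975, 20 df)·SD·√(2/11). At SD 1.212 this is 2.086 × 1.212 × 0.4264 = 1.08 points; at SD 1.149 it is 1.02.

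**5. If the noninferiority label were taken literally.** With 11 per arm and a true difference of 0, the margin giving 90% power (noncentral t) is 1.67 to 1.76 at one-sided 0.025, and 1.49 to 1.57 at one-sided 0.05, over the same SD range. Sample size does not state sidedness. The assumed benefit over control is 1.65 to 1.70, so the margin would be roughly as large as the whole effect. With an illustrative margin of 0.5 at one-sided 0.025 (normal approximation), power is 16% to 17%, and 90% power would need 111 to 124 per arm.

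**The case against.** The strongest reply is that exercise versus exercise may not be the main comparison. The Abstract compares the exercise groups with control, the Background asks whether each programme works through this medium, and the sentence after the objective in the Aim asks whether the intervention is effective. On that reading the sample size is reasonable: at the implied SD each contrast with control has 86% to 91% power at 11 per arm. This stands. The primary contrast is inconsistent between sections, and the point does not rest on the Aim alone.

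Three stronger readings are tempting, and the article does not support them:
- *That the 90% belongs only to an omnibus F-test.* The article names software, not a test, and the contrasts with control come close to 90% as well.
- *That any workable noninferiority margin must exceed the whole assumed effect.* That is true at the upper SD with one-sided 0.025, but not at one-sided 0.05, where the margin falls below it.
- *That the trial set out to detect 0.05 point.* This is the gap between two planning means, not a declared target. If the true difference were larger, power would be higher than 5%.

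It is also fair that a condensed article may leave the margin and SD to the full protocol, which Statistical analysis mentions. Their absence is therefore not the defect. The conflict between the noninferiority label and the difference tests is in the printed text and remains without them.

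**Conclusion.** The point holds in this form. The noninferiority label contradicts the planned analysis. The stated 90% cannot apply to cycling versus neuromuscular training, for which superiority power at the protocol's own means is about 5% whatever the SD. The sample size instead fits exercise versus control, as the Abstract words it: 86% to 91% per contrast, or 77% to 84% with two contrasts at 0.025 each, at 11 per arm.

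The 5% rests on one assumption, that the 0 is the control mean. The exercise-versus-control powers, the half-width of about 1 point and the margin of about 1.5 to 1.8 points also rest on an SD of 1.15 to 1.21, inferred from a one-way ANOVA that the article does not name.

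**What to change.** - **Sample size:** remove the noninferiority wording, which the planned analysis does not support. State the test and SD actually entered in the software, and say that the 90% does not cover cycling versus neuromuscular training.
- **Aim and Abstract:** reconcile them by naming exercise versus control as the confirmatory comparison. Choose a multiplicity rule for the two contrasts and restate power under it. At the implied SD and 0.025 each, this is about 77% to 84% at 11 per arm; replace these figures with ones based on the real SD.
- **Cycling versus neuromuscular training:** report the estimated difference with its 95% CI (expected half-width about 1 point at the implied SD), and make no superiority, noninferiority or equivalence claim.

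If the investigators do intend noninferiority, they would need a justified margin, a matching analysis and a new sample size. The 0.5-point illustration shows that this could mean more than 100 per arm.

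The recommended route costs only wording and needs no extra patients. Its price is a less favourable stated power and the loss of a formal claim about which exercise is better.

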### Statistical analysis

Statistical analysis is performed using the SPSS software (25.0). Significance level will be set at 0.05 for all statistical analysis. Intention-to-treat principle will be followed. Baseline comparability between groups of categorical variable data was determined using the chi-square test or other suitable nonparametric tests. Quantitative data will be expressed as the mean (SD), if it follows normal distribution and homogeneity of variance; otherwise, median (IQR) is given. For statistical inference, if the data obeyed a normal distribution and homogeneity of variance and satisfied spherical symmetry, variance analysis of repeated measurements was used; otherwise, the Kruskal–Wallis *H* rank sum test will be conducted. For data that recorded from drop-out participants, maximum likelihood estimation will be used to impute missing data, including any lacks for primary and secondary outcomes. The data collected are kept by people not involved in the trial intervention and by the online platform. The datasets analyzed during the current study and statistical code are available from the corresponding author on reasonable request, as it is the full protocol.

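### Wrong as written: failure of any one assumption, sphericity included, replaces the four-visit analysis with a Kruskal–Wallis test that has no time factor

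*Protocol article*

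**What the plan says.** The rule is in the Statistical analysis section of the protocol article. Repeated-measures ANOVA applies under a joint condition: "if the data obeyed a normal distribution and homogeneity of variance and satisfied spherical symmetry, variance analysis of repeated measurements was used". Every other case goes to one alternative: "otherwise, the Kruskal–Wallis *H* rank sum test will be conducted". Nothing stands between the two, such as a degrees-of-freedom correction, a mixed model or a rank method for repeated measures. The same section sets the level: "Significance level will be set at 0.05 for all statistical analysis".

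Other sections fix the setting. Outcome assessments gives four time points: baseline and weeks 4, 8 and 12. Primary outcome measures lists two primary outcomes, WOMAC and an 11-point pain scale. WOMAC items are scored 0 to 4, so the five-item pain subscale is a bounded whole-number score from 0 to 20. Sample size works with reductions in WOMAC pain ("The average pain scores in patients with KOA were 1.65, 1.7, and 0 respectively"), 33 evaluable participants and 14 enrolled per group.

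**The concern.** Three things are wrong with the rule, and none of them depends on a simulation.

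- **The fallback answers a different question.** Kruskal–Wallis compares independent groups on one value per person. It cannot test whether the arms diverge over the visits and it takes no covariate. The section does not name the visit, or say whether the raw score or the change is used, so the primary analysis is undefined once the switch is made.
- **The remedy does not match the failure.** Sphericity concerns the covariance between visits, not the shape of the distribution. Ranking one value per person discards the repeated structure instead of allowing for it.
- **The outcome data choose the primary test.** WOMAC and the pain scale could pass and fail different checks and so be analysed by different methods in the same report.

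At stake is whether the primary result is a pre-specified analysis of the 12-week course, and some power in a trial of 42 people.

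**Working it through.** **1. The logic of the rule.** Repeated-measures ANOVA requires normality AND equal variance AND sphericity. The complement is failure of at least one. Sphericity failing on its own is therefore enough to trigger Kruskal–Wallis.

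**2. The plan's own figures.** The article states: "A total of 33 participants is required for the calculation". Enrolment reproduces: 33 / 0.80 = 41.25, rounded up to 42; per arm 11 / 0.80 = 13.75, rounded up to 14. The 33 cannot be checked directly, because no SD is given. It can be solved backwards:
- The mean of 1.65, 1.70 and 0 is 1.117, with deviations 0.533, 0.583 and −1.117.
- The SD of the means is √[(0.284 + 0.340 + 1.247) / 3] = 0.790.
- A one-way three-group ANOVA at alpha 0.05 and 90% power with N = 33 needs f = 0.652, so SD = 0.790 / 0.652 = 1.21.

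This SD of change is an assumption used below, not a figure from the article.

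**3. Sphericity check alone** (simulated normal data, Mauchly's test at 0.05, pooled within-group covariance, four visits):

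| Assumed correlation between visits | 42 patients | 33 patients |
|---|---|---|
| Compound symmetry | about 5% | about 5% |
| AR(1), adjacent 0.5 | about 63% | about 50% |
| AR(1), adjacent 0.6 | 79% | 65% |
| AR(1), adjacent 0.7 | 90–91% | 79% |
| AR(1), adjacent 0.8 | 95–96% | 88% |
| AR(1), adjacent 0.9 | 98–99% | 95% |

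**4. Any check failing** (Shapiro–Wilk, Levene and Mauchly, each at 0.05; 11 or 14 per arm). The article does not say how the assumptions will be tested, so the number of checks is varied.
- All assumptions true (normal data, compound symmetry with correlation 0.5): 60–63% with 12 arm-by-visit normality tests, four Levene tests and Mauchly; 38–40% with four residual normality tests instead; 15–17% with one normality test, one Levene test and Mauchly.
- Normal data, AR(1) 0.5 to 0.85: 52–99%.
- Scores rounded and limited to 0–20: 56–99% under AR(1), 16–72% under compound symmetry.
- Skewed 0–20 scores: 54–100%.

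**5. Power at week 12** (11 per arm, mean reductions 1.65, 1.70 and 0, change SD 1.21). The baseline-to-week-12 correlation is 0.8³ = 0.51 or 0.9³ = 0.73:

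| Analysis | Correlation 0.51 | Correlation 0.73 |
|---|---|---|
| Kruskal–Wallis, raw score | 86–87% | about 61% |
| Kruskal–Wallis, change | 86–88% | 86–88% |
| One-way F test, change | 90–91% | 90–91% |
| Baseline-adjusted ANCOVA | 96% | 92–94% |

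The raw-score row falls because the change SD is held fixed. Raw SD = 1.21 / √[2(1 − r)], which is 1.22 at r = 0.512 and 1.64 at r = 0.729.

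**The case against.** The strongest reply concerns size, and most of it stands.

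- **Frequency.** A reader might infer that the switch will happen in most realistic datasets. The documents do not support that as a fact: they give no correlation structure, no score distribution and no account of how the assumptions are checked. Correlation that decays over visits 4 weeks apart is a reasonable expectation, but it remains an assumption. With compound symmetry, near-normal scores and few checks, the switch rate is about 15%.
- **Power.** A reader might infer a loss of about 32 points from 61% against 93% at correlation 0.73. That contrast assumes raw week-12 scores. Sample size speaks of reductions in pain and the abstract of differences between before and after treatment, so change from baseline is the likelier variable. On change, ranks alone cost about 3 to 4 points against the F test. The gap to ANCOVA is about 6 points (92 − 86) to 9 points (96 − 87). ANCOVA is also a yardstick, not the protocol's first choice; the power of the planned repeated-measures ANOVA was not computed.
- **Baseline.** It would be too strong to say that the fallback cannot use baseline. Run on change scores, it does, and it can compare change between arms at a given visit. What it lacks is the joint group-by-time test and covariate adjustment.
- **Detail left elsewhere.** An article may leave detail to the full protocol. That does not answer this point, because the article states the rule outright and the rule as stated is wrong.

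**Conclusion.** The decision rule is wrong as written. A failed sphericity check should not lead to Kruskal–Wallis; the fallback's visit and score are not named; and the primary test is selected from the trial's own outcome data. These conclusions follow from the text and need no assumption.

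The size is conditional. Mauchly's test alone would reject in about 63–99% of trials of 42 patients under AR(1) correlation of 0.5 to 0.9, but in about 5% under compound symmetry. The overall switch rate spans about 15% to nearly 100%. The power cost is modest if the fallback uses change (about 86–88% against 92–96% for ANCOVA). It is large only if raw scores are used and the baseline correlation is high (61% at 0.73). All power figures rest on normal data, 11 per arm and the back-solved change SD of 1.21.

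**What to change.** Replace the conditional rule with one primary analysis, named in advance and not dependent on preliminary tests.

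- **Minimum:** keep repeated-measures ANOVA and apply a Greenhouse–Geisser correction when sphericity fails. This removes the sphericity trigger within the stated method. Also drop normality and equal variance as conditions for switching the primary test.
- **Preferable:** a mixed model on weeks 4, 8 and 12 with baseline score, arm, visit and arm-by-visit. It is available in SPSS MIXED and agrees with the maximum-likelihood handling of missing data already stated. Other fixed choices would also do.
- **Sensitivity analysis only:** Kruskal–Wallis on change from baseline at week 12, with that visit and score written down.

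Apply the same method to WOMAC and the 11-point pain scale. The cost is one paragraph of text; the software, data, visits and sample size stay as they are.

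### The analysis section names only three-arm omnibus tests while the objectives concern specific arms, and the stated 90% power does not carry over to those comparisons

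*Protocol article*

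**What the plan says.** The Aim is about two named arms: "The primary objective of this study is to compare the effect of IoT-based power cycling and neuromuscular training on the elderly patients with KOA". The Methods part of the Abstract adds a second question, how the exercise participants differ from the control group before and after treatment.

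For inference, the Statistical analysis section says that "if the data obeyed a normal distribution and homogeneity of variance and satisfied spherical symmetry, variance analysis of repeated measurements was used"; if those conditions fail, a Kruskal–Wallis test replaces it. Every test is at 0.05. Allocation is 1:1:1 to three arms, so every test of group or group-by-time from that ANOVA is a three-arm test, as is Kruskal–Wallis.

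The Sample size section refers to "the calculation requirements of the sample size of noninferiority experiments" and gives no margin. It states that "The average pain scores in patients with KOA were 1.65, 1.7, and 0 respectively", without tying the figures to arms, and sets alpha and power ("We set a to 0.05 and test power 1-β to 90"%). It concludes: "A total of 33 participants is required for the calculation". Twenty per cent dropout takes this to 14 enrolled per arm. No SD is given, and no test is named beyond "Calculation via G*Power 3.1 software".

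**The concern.** An omnibus test asks whether the three means are all equal. Rejecting that says only that some arm differs from some other. The trial asks something narrower: does each programme beat control, and how do the two programmes compare?

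If the result is reported from the omnibus test alone, an inert programme could be credited with the effect of the other one, or a significant F could be taken as a ranking of the two programmes. The single power figure would also be read as the chance of answering the objective, although the comparisons that the objective needs have different power.

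**Working it through.** **Inputs.** From the Sample size section: means 1.65, 1.70 and 0, alpha 0.05, power 90%, 33 evaluable participants (11 per arm), 20% dropout. Assumptions: the first two means are the exercise arms and the third is control; the calculation was a one-way ANOVA F test. The SD is not given and is solved for below.

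**1. The plan's own figure.** The 33 cannot be recomputed from the stated inputs because the SD is missing. For a one-way F test (df 2 and 30), the noncentrality is λ = n·Σ(μᵢ − μ̄)² / SD². For 1.65, 1.70 and 0, μ̄ = 1.1167 and Σ(μᵢ − μ̄)² = 0.2844 + 0.3403 + 1.2469 = 1.872. Exactly 90% power at n = 11 requires SD = 1.212, so λ = 11 × 1.872 / 1.469 = 14.0 and f = 0.652. Eleven per arm is the smallest size reaching 90% for an SD between 1.15 and 1.21. The dropout step agrees: 33 / 0.8 = 41.25, rounded up to 42 = 3 × 14.

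**2. One programme works, or both: algebra.** Let the effect be d.
- Both work (d, d, 0): Σ = (d/3)² + (d/3)² + (2d/3)² = 2d²/3.
- One works (d, 0, 0): Σ = (2d/3)² + (d/3)² + (d/3)² = 2d²/3.

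The sums are the same, so λ and the power are the same for any SD and any n.

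**3. With the planned means (11 per arm).**

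| Means | Σ | Power, SD 1.212 | Power, SD 1.15 |
|---|---|---|---|
| 1.65, 1.70, 0 | 1.872 | 90.0% | 92.9% |
| 1.70, 0, 0 | 1.927 | 90.9% | 93.6% |
| 1.65, 0, 0 | 1.815 | 89.0% | 92.2% |

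**4. The tests actually named** (SD 1.212).
- Group-by-time F, assuming linear change and a correlation of 0.5 between visits: 82.9% if both work, 81.6–84.2% if one does.
- Kruskal–Wallis, simulated: 88.0% if both work, 88.7% for 1.70, 0, 0.

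The level moves, but the near-equality stays.

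**5. Power for the contrasts** (11 per arm, SD 1.212, two-sided 0.05). The standard error of a difference is 1.212 × √(2/11) = 0.517. The noncentralities are 1.65/0.517 = 3.19, 1.70/0.517 = 3.29 and 0.05/0.517 = 0.10.

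| Contrast | Ungated, pooled variance (30 df) | Gated by omnibus test (simulated) |
|---|---|---|
| 1.65 arm vs control | 87% | 84% |
| 1.70 arm vs control | 89% | 86% |
| Both vs control | – | 80% |
| Exercise vs exercise (0.05) | 5% | 5% |

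The last row is essentially alpha, and it stays at 5.1% ungated if all 14 per arm are followed. The 95% CI for any pairwise difference has a half-width of about 2.04 × 0.517 = 1.06, against a planned exercise-versus-exercise difference of 0.05.

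**6. What a significant omnibus result leaves open** (simulated). If both programmes work, 79.9% of trials have both control contrasts significant, against 90.1% with a significant omnibus test. So about 11% of significant results lack at least one of the two contrasts. If only one works (1.70, 0, 0), the omnibus test is significant 90.9% of the time, but the inert arm's own contrast with control only about 5%.

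**The case against.** The strongest reply is that contrasts after an ANOVA are routine, that this is a condensed article, and that they may be set out in a full protocol or analysis plan not shown here. That stands: the mere absence of a post hoc procedure is not the point. Nor does the article say that arms will not be compared; its Abstract and Aim say that they will.

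A reader might infer that the omnibus test is the only inference planned, or that the design cannot answer its objective. The documents support neither. Pairwise differences come from the same repeated-measures model, and other documents may specify them.

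A reader might also take 90% as the power of the named repeated-measures or Kruskal–Wallis test. That is not supported either: the figure is tied to a one-way F test only by assumption, and step 4 gives other levels. Finally, no passage proposes to read a significant F as proof that both programmes work, and on the planned means about 89% of significant omnibus results do have both control contrasts significant.

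What remains is visible in the published text. It fixes an omnibus inference and one power figure, while its questions concern named arms. The noninferiority reference does not close the gap, because no margin is given and no matching analysis is named.

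**Conclusion.** The point holds as a mismatch between the named inference and stated power on one side and the objectives on the other. A significant three-arm test does not separate one effective programme from two, and it does not rank the two. That equality of power is exact for equal effects, within about one percentage point for the planned means under the one-way test, and independent of the SD.

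The power levels are conditional. They assume a one-way F test, 11 evaluable per arm, the means read as two exercise arms then control, and an SD of 1.21 solved from the plan's own total. On that basis the stated 90% is not the power for the objectives: it is about 84% and 86% for the gated contrasts with control, 80% for both, and about 5% for superiority of one programme over the other. Power for a noninferiority comparison cannot be given without a margin.

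**What to change.** **Statistical analysis section.**
- Make the primary result the three pairwise differences from the same model (cycling minus control, neuromuscular minus control, cycling minus neuromuscular), each with a 95% CI, at one prespecified time point. Week 12, the end of the intervention, is an example.
- Use the three-arm test at that same time point, at 0.05, as a gate, then test the pairs at 0.05. With exactly three arms, either all means are equal, and the gate holds the error at 5%, or at most one pair is equal, and it is tested at 5%. Family-wise error is thus controlled for one outcome.
- WOMAC and the 11-point pain scale are both primary, so state separately how the two are handled.
- Call a programme effective only if its own contrast with control is significant.
- If Kruskal–Wallis stays as the fallback, name its pairwise counterpart.

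**Sample size section.** State the SD, the test and which mean belongs to which arm. Restate the power for the contrasts, and say that the trial is not powered to show superiority of one exercise programme over the other.

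**Cost.** Wording in two sections, with no extra patients or data. The downside is less favourable quoted power: about 84–86% per contrast with control, and an open statement that the head-to-head comparison is estimated rather than powered.

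### Imputing dropouts by maximum likelihood and then running repeated-measures ANOVA or Kruskal–Wallis would, on the natural reading, treat filled-in values as observed

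*Protocol article*

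**What the plan says.** All of this stands in the protocol article, Statistical analysis and Sample size sections.

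- **Missing outcomes.** For participants who drop out, "maximum likelihood estimation will be used to impute missing data, including any lacks for primary and secondary outcomes".
- **Tests.** If normality, equal variance and sphericity hold, "variance analysis of repeated measurements was used"; otherwise a Kruskal–Wallis "rank sum test will be conducted". No other inferential method is named for the outcomes.
- **Principle and level.** "Intention-to-treat principle will be followed", and "Significance level will be set at 0.05 for all statistical analysis".
- **Expected loss.** The target of 33 evaluable participants is raised "With allowance for a dropout rate of 20"%, to 14 per group (42 in all).

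Outcomes are measured at baseline and at weeks 4, 8 and 12. The article names no mixed model, no multiple imputation and no pooling rule.

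**The concern.** Maximum likelihood is a way of estimating parameters from incomplete data. It can be used without filling anything in, by fitting a model to whatever was observed. The article instead says it will be used to impute, and follows it with two tests that have no means of carrying imputation uncertainty. Standard repeated-measures ANOVA needs complete rows, and Kruskal–Wallis is rank-based and has no likelihood. Predicted values placed in the gaps would therefore count as full observations.

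The harm depends on a point the article leaves open:

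- **Arm in the imputation model.** Dropouts are placed exactly where their arm's model predicts. Residual variation is understated, the sample size is overstated, and false positives rise.
- **Arm not in the imputation model.** Dropouts from all arms are given the same kind of prediction, which pulls the arms together and shrinks the estimated effect.

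The sentence covers every primary and secondary outcome, and it is how the intention-to-treat analysis would be delivered.

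**Working it through.** **1. The plan's own dropout figure.** 33/3 = 11 evaluable per arm, and 11/(1 − 0.20) = 13.75, rounded up to 14 per arm, or 42 in total. This reproduces the stated figure. It corresponds to 3 dropouts in 14 (21%) per arm.

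**2. Arm included: a case that can be done by hand.** Take a baseline-adjusted comparison of two arms at week 12, with d dropouts per arm who have only a baseline value. The maximum-likelihood fill-ins lie exactly on the line fitted to the observed participants, so they add nothing to the residual sum of squares. They do raise the apparent degrees of freedom to 42 − 4 = 38 and the apparent arm size to 14. With m = 14 − d observed per arm and true residual degrees of freedom 3m − 4:

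reported SE / true SE ≈ √[ (3m − 4)/38 × m/14 ]

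The test rejects when |t| exceeds 2.024 (38 df), which in truth is a cut-off of 2.024 × ratio on 3m − 4 df.

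| d per arm | m | true df | SE ratio | effective cut-off | type I error |
|---|---|---|---|---|---|
| 1 | 13 | 35 | 0.925 | 1.872 | 7.0% |
| 2 | 12 | 32 | 0.850 | 1.720 | 9.5% |
| 3 | 11 | 29 | 0.774 | 1.568 | 12.8% |

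Simulation of the same contrast with 3 dropouts per arm (correlation 0.3, 0.5 or 0.7; early or spread dropout) gave 11.3–13.9%, with reported SEs 20–25% too small. For example, at correlation 0.5 with early dropout, the mean reported SE was 0.34 against a true 0.45.

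**3. Arm included: the test the article names.** Simulation used 14 per arm, four visits, compound symmetry with correlation 0.3–0.7, and monotone dropout completely at random. Type I error of the group-by-time test, nominal 5%:

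| Dropouts per arm | Type I error |
|---|---|
| 1 | about 6–9% |
| 2 | about 7–12% |
| 3, spread over weeks 4–12 | about 12–17% |
| 3, all before week 4 | up to 24% |

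A one-way ANOVA of week-12 change with 3 dropouts per arm gave about 10–14%. With full data or completers only, type I error for both tests was about 5–6%.

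**4. Arm left out.** If dropouts contribute only a baseline value, randomisation makes their predictions equal across arms on average, so the expected difference is the true one times m/14. Using the article's planning difference between the first and third groups, 1.65 − 0 = 1.65, this gives 1.65 × 11/14 = 1.30, a dilution of 3/14 = 21%. Simulation gave 1.28–1.37, that is 17–22%, with the smaller losses when dropout is spread over visits. Type I error stayed at about 5–6%. Power for group by time was about equal to or below completers only (for example 73.8% against 76.8% at correlation 0.5 with early dropout).

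**5. With imputation uncertainty carried through.** Multiple imputation with arm in the model (20 imputations, Rubin's rules, week-12 baseline-adjusted contrast) gave a type I error of 3.7–4.7%. Mean SEs were 0.37–0.52, against a true 0.36–0.51.

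**The case against.** **The wording may be loose.** The article does not say single imputation, conditional mean or one completed dataset, and the phrase could be shorthand for a likelihood fit to incomplete data. This stands in part: a single fill-in is an inference. It is still the natural reading, because the verb is to impute, no model that could use a likelihood directly is named, and the fallback is a rank test.

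**This is detail for a fuller document.** The variables in the imputation model and the pooling method are indeed normally found there, and their absence is not the point. The point is that the stated pairing of method and tests does not work on its natural reading.

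**The 20% is a margin, not a forecast.** This stands. With one dropout per arm the inflation is modest, which is why the sizes are shown by dropout level.

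**Stronger readings that the article does not support.** A reader might infer that false positives are certain to be inflated. They are not: without arm in the imputation model the error rate stays near nominal and the cost is dilution, which is conservative for showing a difference. The article does not say which applies. A reader might also infer that confidence intervals will be too narrow, but the article plans none. Nor is the lack of a delta-adjusted sensitivity analysis an error.

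**Conclusion.** The concern holds on the natural reading of the Statistical analysis section: a maximum-likelihood fill-in followed by tests that treat the filled-in values as data. The two harms are alternatives, and neither size is a known property of this plan until the imputation model is stated.

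The sizes rest on assumed visit correlations, compound symmetry, normal data and dropout completely at random, because the article gives no SD, correlation or dropout pattern. The direction did not change across the range tried. Bias from outcome-related dropout is not included. The Kruskal–Wallis branch was not simulated; the objection there is that it too would count imputed values as observations.

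This should be corrected before analysis. It does not touch recruitment, visits or data collection.

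**What to change.** Replace the imputation sentence and the repeated-measures ANOVA with a likelihood-based repeated-measures mixed model (arm, visit, arm by visit), fitted directly to all observed visits of all randomised participants, with no filled-in values. It is valid if data are missing at random and is available in the named software, SPSS 25. It was not simulated here at 14 per arm.

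Where a filled-in analysis is kept, use multiple imputation with arm in the imputation model and pool the between-arm contrasts by Rubin's rules. Those rules combine estimates and variances; they do not directly pool an omnibus F or a Kruskal–Wallis statistic. Do not run Kruskal–Wallis on singly imputed values.

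The cost is slightly more analysis work and somewhat larger, but honest, standard errors. A delta-adjusted sensitivity analysis is optional and not part of this correction.
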